### Participant timeline {13}

The participant timeline is presented in Fig. 1.

**Fig. 1 Fig1:**
[figure not shown]
The schedule of enrolment, interventions, and assessments

### Sample size {14}

According to published studies, the mean oxygen saturation in control groups during intubation has been found to be 88% [21]. We posit that the intervention group may be increased by 5% and that the standard deviation will be 12%. Using a two-tailed α = 0.05, and β = 0.20, the sample size of the intervention group and control group were calculated using PASS 11 software to be N1 = N2 = 72 cases, or 144 cases total.

### Recruitment {15}

This study is expected to be carried out over 12 months. Patient recruitment and data collection will take place over a period of 10 months, from July 10, 2020, to May 10, 2021. An additional 2 months is being allocated for statistical analysis and write-up.

## Assignment of interventions: allocation

### Sequence generation {16a}

SPSS software will be used to generate the corresponding number of random sequences according to the sample size. And then, the random values will be divided equally into two groups as the control group and the intervention group. Patients involved in this research will be randomly assigned to these two groups. The grouping arrangement will not be changed once the research project is underway.

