## Methods: participants, interventions, and outcomes

### Study setting {9}

This study will be led by the Emergency Department of Peking Union Medical College Hospital in Beijing, China. Three other hospitals will also enroll patients, including the First Affiliated Hospital of Xinjiang Medical University in the Xinjiang Uygur Autonomous Region, the Second People’s Hospital of Huai’an, and the Suqian People’s Hospital in Jiangsu province in China. These are all grade III A hospitals with adequate medical consultants, qualified doctors, and monitoring equipment to fulfill this study.

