### Implementation {16c}

Participating units will be trained to familiarize the study protocol, appoint a project manager, and obtain data collecting form in the launching conference. The manager in each unit will allocate the form to clinicians and supervise the research progress.

Patients will be selected based on their clinical characteristics and eligibility criteria by clinicians. After confirmation of inclusion, the clinician will contact the statisticians who generate the random sequence and access the grouping information. Then, they will assign the subjects to the intervention or control group accordingly and collect relative data.

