### Interim analyses {21b}

If the intervention group shows any clear harms to patients (e.g., a statistically higher incidence of complications), the study will be terminated early. A check for elevated risk will occur at 6 months by the endpoint adjudication committee (see below).

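### The allocation described has no blocks or hospital strata and the primary test ignores hospital: a small, avoidable loss of precision and of within-hospital balance, not a bias

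*Protocol article*

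**What the plan says.** The article states a method for the sequence and does not defer it to another document. Under Sequence generation {16a}, "SPSS software will be used to generate the corresponding number of random sequences according to the sample size", after which "the random values will be divided equally into two groups as the control group and the intervention group". Sample size {14} sets the length of the list: "N1 = N2 = 72 cases, or 144 cases total". No block or stratum is mentioned.

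Study setting {9} names a lead hospital in Beijing and adds that "Three other hospitals will also enroll patients". It gives no expected enrolment per hospital. Under Implementation {16c}, "the clinician will contact the statisticians who generate the random sequence and access the grouping information". That fits one central list, although the article never says so outright.

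The section on analysis of the primary outcome compares lowest SpO2 between arms by a t-test or a rank-sum test, with no hospital term. The complication rates are compared by chi-square or Fisher tests, also without hospital. Interim analyses {21b} adds: "A check for elevated risk will occur at 6 months".

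**The concern.** One equal split of 144 values fixes the arm totals only at the end of the list. It does not control the arms within a hospital. Nor does it fix them exactly at the 6-month check, or at the end if recruitment, which closes on a calendar date, stops short of 144.

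Lowest SpO2 during laryngoscopy could plausibly vary with case mix, the bagging team, the intubator and the monitor, and these may differ between hospitals. If so, chance differences in the hospital make-up of the arms add noise to the comparison, and neither the allocation described nor any stated analysis removes it. At stake are some precision on the primary outcome and a baseline table that may show a small hospital with lopsided arms.

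**Working it through.** **Inputs from the article.** Sample size {14} gives "Using a two-tailed α = 0.05, and β = 0.20". It also gives the effect and spread: "We posit that the intervention group may be increased by 5% and that the standard deviation will be 12" (percentage points). The list holds 144 values split 72:72, four hospitals enrol, recruitment lasts 10 months, and the harm check is at 6 months.

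**Assumptions, because the article gives no figure.** These are the hospital sizes, even accrual, and the share of outcome variance explained by hospital (ICC, 0.05 to 0.15).

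**1. The plan's own figure.** For two means, n per arm = 2(z₁ + z₂)²σ²/δ².
- Two-sided 0.05: 2 × (1.960 + 0.842)² × 144/25 = 90.4, so 91 (92 by noncentral t).
- One-sided 0.05: 2 × (1.645 + 0.842)² × 144/25 = 71.2, so 72.

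The stated 72 therefore does not follow from the stated two-tailed alpha. It matches a one-sided test. At 72 per arm the two-sided t-test has 70.0% power, and that is the baseline used below. The mismatch is a separate matter and does not alter the allocation point.

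**2. Balance within a hospital.** Under a 72:72 split, the number assigned to one arm among any n patients is hypergeometric(144, 72, n).
- n = 20: SD 2.08, 95% range 6:14 to 14:6. P(13:7 or worse, either way) = 2 × 0.114 = 22.8%.
- n = 36: 95% range 13:23 to 23:13. P(2:1 or worse) = 3%.
- n = 10: 95% range 2:8 to 8:2. P(2:1 or worse) = 33%.

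Simulated chance (20,000 permutations) that at least one of the four hospitals is 65:35 or worse: 12% for 36/36/36/36 and 44% for 72/32/20/20. At 2:1 or worse it is 12% for four equal hospitals, 31% for 72/24/24/24, 24% for 84/20/20/20 and 48% for 100/20/14/10.

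**3. Overall balance at the 6-month check.** With even accrual, 144 × 6/10 ≈ 86 patients.
- SD of the arm count 2.95; 95% range 37:49 to 49:37; mean absolute difference 4.7.
- P(difference of 10 or more) = 12.6%; P(60:40 or worse) = 0.4%; P(2:1 or worse) is below 0.01%.
- Standard error at 37:49 relative to 43:43: √[(1/37 + 1/49)/(2/43)] = 1.010, a 1% increase.
- For an illustrative harm of 10% vs 30%, power is 64% at 43:43 and 62% to 65% at 37:49, depending on which arm is larger.

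**4. What the remedy gains on the primary outcome.** With hospital in the model, the residual SD is 12 × √(1 − ICC). Perfect within-hospital balance has efficiency 1. The existing 72:72 list with hospital in the model has mean efficiency 97.9% (2.5th percentile about 93.5%).

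| ICC | Residual SD | No stratification, no adjustment | Hospital term only | Hospital term and balanced strata |
|---|---|---|---|---|
| 0.05 | 11.70 | 70.0% | 71.2% | 72.2% |
| 0.10 | 11.38 | 70.0% | 73.5% | 74.5% |
| 0.15 | 11.06 | 70.0% | 75.9% | 76.8% |

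The last two columns differ by about 0.9 points. That is the contribution of the blocks, and the rest comes from the hospital term.

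**5. What blocks do to balance.** Blocks of 4 within hospital hold the difference to at most 2 in any hospital; blocks of 6 hold it to at most 3. With about 60% of patients enrolled, the mean absolute overall difference falls from 4.7 to about 1.4 (blocks of 4) or 1.7 (blocks of 6). The 97.5th percentiles are 4 and 5.

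**The case against.** An equal split without blocks is valid randomisation, and the tests planned on it keep their error rate, because chance imbalance by hospital is part of the variation that they already allow for. This stands: the point concerns efficiency and presentation.

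The single list is inferred. Numbered envelopes could be kept at each hospital, and a journal article may leave block sizes to the full protocol. This stands in part. The point should be worded as a reading of the method described. But that method is stated, with an equal division as its only restriction, so the point does not rest on silence alone.

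The hospital sizes, cut-offs and ICC are chosen by the reader. All four hospitals are of the same grade, intubators need at least 3 years of experience, and ventilation is monitored for consistency, so differences between hospitals may be small. This also stands, and it is why ranges are shown. A low ICC would shrink the gain.

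Two stronger readings are tempting. A reader might infer that the arms could be badly unbalanced at the 6-month check, so that a harm signal is created or hidden. The figures do not support this. The 72:72 constraint keeps the totals near 43:43, the edge of the 95% range costs about 1% in standard error, and the check compares incidence, not counts. A chance surplus of one hospital's patients in one arm adds noise, but no inflated false-positive risk follows. A reader might also credit the whole rise in power to stratified blocks, when about 1 point belongs to them.

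**Conclusion.** The point holds as a low-priority design improvement. As described, allocation is balanced only over the full list and the primary test ignores hospital. Visible imbalance in the smaller hospitals is therefore quite possible (12% to 48% for at least one hospital at 2:1 or worse, across the assumed size patterns), and some precision is left unused. For the primary outcome, the combined gain is about 2 to 7 percentage points of power at 72 per arm if hospital explains 5% to 15% of the variance, mostly from adjustment.

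No bias, invalid test or material threat to the harm check follows. The conclusion rests on the natural reading that one list serves all four hospitals, and on assumed hospital sizes, even accrual and an assumed ICC. Blocks would limit imbalance, not abolish it, because incomplete blocks in four strata still leave small differences.

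**What to change.** Generate the sequence in permuted blocks of randomly varying size (for example 4 and 6) separately for each of the four hospitals, and say so in Sequence generation {16a}. Include hospital as a term in the primary analysis of lowest SpO2; without it the gain in precision is largely unused. If the full protocol already stratifies by hospital, state that in the article and add only the hospital term.

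The cost is four short lists in place of one from the same software, and one extra model term. The downside is slightly more predictable allocation within blocks. Random block sizes and the concealment already planned (opaque sealed envelopes, with devices of identical appearance) limit this. If the sample size is revised because of the alpha mismatch, the list length should be revised with it.

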### Concealment mechanism {16b}

Sequentially numbered, opaque, sealed envelopes will be used to conceal the sequence until interventions are assigned.

### Implementation {16c}

Participating units will be trained to familiarize the study protocol, appoint a project manager, and obtain data collecting form in the launching conference. The manager in each unit will allocate the form to clinicians and supervise the research progress.

Patients will be selected based on their clinical characteristics and eligibility criteria by clinicians. After confirmation of inclusion, the clinician will contact the statisticians who generate the random sequence and access the grouping information. Then, they will assign the subjects to the intervention or control group accordingly and collect relative data.

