## Assignment of interventions: blinding

### Who will be blinded {17a}

This will be a double-blind study. Neither patients, nurses, nor physicians performing BVM ventilation or intubation will know which BVM device will be used. To prevent any bias, identical-appearing BVM set-ups with either a 10-mm H2O of PEEP or a 0-mm H2O of PEEP valve will be used according to a patient’s group assignment.

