### Procedure for unblinding if needed {17b}

Unblinding is not allowed unless multiple significant adverse events occur, and termination of the study is considered.

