## Data collection and management

### Plans for assessment and collection of outcomes {18a}

Before randomization, some basic information will be recorded: patient identification number, age, sex, height, weight, body mass index, primary diagnosis, reason for intubation, systolic blood pressure, vasopressor use before intubation including the type and dosage, and any oxygen therapies used, including FiO_2_ and duration of use, pulse oximetry (SpO_2_) before intubation, and recent blood gas analysis (pH, PaO_2_, arterial carbon dioxide partial pressure (PaCO_2_)); any history of a difficult airway, airway evaluation using the MACOCHA score, and the time since the patient’s last meal will be recorded.

According to this basic information, patients who meet eligibility criteria will be randomized. A member of the research staff will select the corresponding BVM device for use prior to intubation. During the procedure, another member of the research staff will record key data. For example, the induction medicine (including drug name and dosage), the duration of BVM ventilation, the SpO_2_ before inserting the laryngoscope, the duration between inserting the laryngoscope and 2 min after intubation, the number of intubation attempts, the lowest SpO_2_ during the procedure, the lowest systolic blood pressure, any vasopressor use, and any incidence of aspiration or cardiac arrest.

During prophylactic BVM ventilation, some additional parameters will be monitored. Data such as exhaled tidal volume, respiratory rate, exhaled oxygen concentration, and partial pressure of end-tidal carbon dioxide will be collected to guarantee consistent manipulation and avoid bias caused by improper operation.

Intubation will be performed by physicians with at least 3 years of previous intubation experience to ensure patient safety. All data will be recorded in the Case Record Form and managed by the ResMan clinical trial public management platform. After collection, data will be analyzed by the statistician in our research group.

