## Statistical methods

### Statistical methods for primary and secondary outcomes {20a}

Data processing will be performed by the statistician in our research group and analyzed under an intention-to-treat premise. A two-tailed p-value less than 0.05 will be defined as statistically significant.

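### The implementation text gives the allocation to the party that also collects the data, which conflicts with the double blind and with the separate staff roles described elsewhere

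*Protocol article*

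**What the plan says.** Five sections of the protocol article bear on who knows the allocation.

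- **Concealment mechanism {16b}:** "Sequentially numbered, opaque, sealed envelopes will be used to conceal the sequence until interventions are assigned".
- **Implementation {16c}:** "Patients will be selected based on their clinical characteristics and eligibility criteria by clinicians". The project manager in each unit hands the data collection form to the clinicians. After inclusion is confirmed, "the clinician will contact the statisticians who generate the random sequence and access the grouping information". The next sentence is "Then, they will assign the subjects to the intervention or control group accordingly and collect relative data". No envelope is mentioned here.
- **Who will be blinded {17a}:** the trial is called double-blind. "Neither patients, nurses, nor physicians performing BVM ventilation or intubation will know which BVM device will be used". The two set-ups look identical and differ only in the valve. The person recording outcomes is not listed.
- **Procedure for unblinding {17b}:** "Unblinding is not allowed unless multiple significant adverse events occur, and termination of the study is considered".
- **Plans for assessment and collection of outcomes {18a}:** "A member of the research staff will select the corresponding BVM device for use prior to intubation". A different member of the research staff records the key procedural data, including lowest SpO2 and aspiration.

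**The concern.** Identical-looking devices protect the blind only if nobody who treats or records is told the arm. Section {16c} appears to tell a clinician the arm at every enrolment, and it gives data collection to the same party.

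The outcomes leave room for influence. The primary outcome in {12} is the lowest SpO2 noted from pulse oximetry during intubation and for 2 minutes afterwards. Aspiration is a visual judgement at laryngoscopy. If someone giving care also knew the arm, {11a} leaves latitude in ventilation rate (12–20 breaths per minute) and {11d} permits other airway interventions. Knowledge of the arm could therefore act on what is recorded and, less certainly, on how the patient is managed.

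There is a practical problem too. Four hospitals have to carry out this procedure, and the protocol gives them accounts that cannot all be followed.

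**Working it through.** No arithmetic applies. The check sets the sections side by side on four questions.

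**1. Who receives the allocation?** In {16c}, on the natural reading, it is the clinician who has just confirmed inclusion. In {18a} it must be at least the staff member who selects the device. In {17a}, nobody who ventilates or intubates may have it.

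**2. Who assigns, and who records?** In the second {16c} sentence, assigning to a group and collecting data share one subject, so whoever assigns also records. In {18a} the two tasks belong to two different people. These accounts are incompatible.

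**3. Does the answer depend on how the sentence is parsed?** Two readings are possible.

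- *The clinician accesses the grouping.* The clinician then enrols, knows the arm, assigns and collects data. That clinicians hold the data collection form supports this reading.
- *The statisticians access the grouping, and the plural pronoun refers to them.* The statisticians, who know the arms, then assign patients and collect bedside data at four hospitals. This is implausible in practice and also contradicts {18a}.

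Under both readings the party that knows the arm collects the data. The conflict with {18a} therefore does not depend on the parse. The conflict with {17a} and {17b} is sharpest under the first reading, because a clinician is told the arm at each enrolment while {17b} reserves unblinding for a possible termination.

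**4. What is the concealment mechanism?** {16b} names envelopes. {16c} names contact with those who generated the sequence. Neither refers to the other. {16c} places the contact after inclusion is confirmed, so the next allocation is not disclosed before the enrolment decision. The statisticians might also hold the envelopes. The two routes are unlinked, but they are not shown to defeat each other.

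**Safeguard check.** {18b} says that some data will be verified against the memory of the patients' monitors. That could correct a misread SpO2 where it is applied. It covers only part of the data, and it cannot correct a judgement about aspiration or a change in care.

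**The case against.** The strongest defence is that the sections can be read together as a workable flow: the clinician confirms eligibility, the allocation is obtained, an unblinded staff member fits the valve, and others ventilate, intubate and record. {17a} expressly blinds the treating staff, {18a} separates the device selector from the recorder, and a condensed article need not spell out every role. The {16c} sentence is also grammatically ambiguous.

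Part of this stands. The design in {16b}, {17a} and {18a} is sound, and the fault lies in the wording of {16c}. But the workable flow requires {16c} to be set aside, because {16c} gives assignment and data collection to one party. That is a stated contradiction, which a fuller document would not excuse.

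A reader might infer more than the text supports:

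- *That allocation concealment fails.* Contact comes after confirmed inclusion, and the statisticians may be the envelope holders.
- *That the treating clinician is unblinded.* {16c} does not say that the enrolling clinician ventilates or intubates. The text only fails to rule it out.
- *That the analyst is unblinded.* {20a} says "Data processing will be performed by the statistician in our research group", but the article does not say that this is the person who generates the sequence. Blinding of the analyst is commonly left to the analysis plan, which is not shown.

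**Conclusion.** The point holds as an internal contradiction about who receives the allocation and who collects the data. Followed as written, {16c} can leave the person recording lowest SpO2 and aspiration aware of the arm. It may also leave a treating clinician aware, if the enrolling clinician goes on to ventilate or intubate, which the protocol neither states nor excludes.

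The size of any bias cannot be computed, since the document gives no basis for saying how far knowledge of the arm would shift the recorded values. The conclusion assumes that sites act on {16c} as worded. If they follow {18a} instead, and the recorder is in fact kept unaware, the harm is largely avoided. On concealment, the finding goes no further than two unreconciled mechanisms.

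**What to change.** 1. State one allocation mechanism, in the same terms, in {16b} and {16c}. If the statisticians hold the envelopes, say so.
2. In {16c}, after inclusion is confirmed, release the allocation only to the device-selecting staff member already named in {18a}. State that this person takes no part in enrolment, ventilation, intubation or recording.
3. Delete from {16c} the wording that gives clinicians the grouping information and has the same party assign patients and collect data.
4. Add the data recorder to the blinded roles in {17a}.

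The cost is protocol wording, circulation to the units and their ethics committees as {25} already provides, and a re-briefing of the four sites. Both staff roles exist in {18a}, so no new role is created.

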## Assignment of interventions: blinding

### Who will be blinded {17a}

This will be a double-blind study. Neither patients, nurses, nor physicians performing BVM ventilation or intubation will know which BVM device will be used. To prevent any bias, identical-appearing BVM set-ups with either a 10-mm H2O of PEEP or a 0-mm H2O of PEEP valve will be used according to a patient’s group assignment.

### Procedure for unblinding if needed {17b}

Unblinding is not allowed unless multiple significant adverse events occur, and termination of the study is considered.

## Data collection and management

### Plans for assessment and collection of outcomes {18a}

Before randomization, some basic information will be recorded: patient identification number, age, sex, height, weight, body mass index, primary diagnosis, reason for intubation, systolic blood pressure, vasopressor use before intubation including the type and dosage, and any oxygen therapies used, including FiO_2_ and duration of use, pulse oximetry (SpO_2_) before intubation, and recent blood gas analysis (pH, PaO_2_, arterial carbon dioxide partial pressure (PaCO_2_)); any history of a difficult airway, airway evaluation using the MACOCHA score, and the time since the patient’s last meal will be recorded.

According to this basic information, patients who meet eligibility criteria will be randomized. A member of the research staff will select the corresponding BVM device for use prior to intubation. During the procedure, another member of the research staff will record key data. For example, the induction medicine (including drug name and dosage), the duration of BVM ventilation, the SpO_2_ before inserting the laryngoscope, the duration between inserting the laryngoscope and 2 min after intubation, the number of intubation attempts, the lowest SpO_2_ during the procedure, the lowest systolic blood pressure, any vasopressor use, and any incidence of aspiration or cardiac arrest.

During prophylactic BVM ventilation, some additional parameters will be monitored. Data such as exhaled tidal volume, respiratory rate, exhaled oxygen concentration, and partial pressure of end-tidal carbon dioxide will be collected to guarantee consistent manipulation and avoid bias caused by improper operation.

Intubation will be performed by physicians with at least 3 years of previous intubation experience to ensure patient safety. All data will be recorded in the Case Record Form and managed by the ResMan clinical trial public management platform. After collection, data will be analyzed by the statistician in our research group.

